### The INCUR study

#### Hypotheses and objectives

The INCUR project is specifically aimed at retrieving data from routine clinical practice in order to estimate the incidence of pneumonia events in older persons living in a sample of French nursing homes. Moreover, INCUR is designed to estimate the clinical and economical consequences of pneumonia events by measuring the subsequent access to medical procedures and resources. More in details, the following hypotheses have driven the rationale and conception of the INCUR project:

Primary hypotheses:

a. Pneumonia is a clinical condition frequently complicating the nursing home stay of older persons;

Secondary hypotheses:

a. The onset of a pneumonia event in institutionalized older residents is associated with higher healthcare costs;

b. Incident pneumonia events are associated with an increased risk of mortality in older persons living in nursing home;

c. The onset of a pneumonia event is responsible for a significant worsening of the physical function of nursing home residents;

Tertiary hypotheses:

a. Specific variables at patient- and nursing home-level may predict the severity of the pneumonia-related functional loss;

b. Nursing home residents dying due to pneumonia produce a significantly higher burden in terms of healthcare costs compared to nursing home residents dying for other causes.

Therefore, the INCUR project will pursue the following aims:

Primary aims:

a. To estimate the incidence of pneumonia events in a sample of older nursing home persons over a period of 12 months;

Secondary aims:

a. To compare the healthcare costs of nursing home older persons experiencing a pneumonia event versus those who will not over a period of 12 months;

b. To calculate the mortality risk in a sample of older residents living in nursing home according to the presence/absence of a pneumonia event occurred during a follow-up period of 12 months;

c. To measure the physical function modifications experienced by a sample of nursing home residents according to the presence/absence of a pneumonia event occurred during a follow-up period of 12 months;

Tertiary aims:

a. To identify sociodemographic, clinical, and biological characteristics of nursing home older residents, as well as environmental and organizational factors of their own hosting institution, which are associated with a higher degree of functional loss following a pneumonia event;

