Each eligible participant will be followed-up for 12 months with a total of three clinical assessments: at baseline, 6 months (mid-term visit), and 12 months (close-out visit). The timeline of the INCUR project is depicted in Figure 1. Recruitment of participants and baseline visits began in February 2012 and ended in July 2012, after a preliminary organization phase (for coordinating activities of researcher with the participating nursing homes). The mid-term visit of participants (after 6 months of follow-up) is currently ongoing.

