### Sample size analyses

Mehr and colleagues [25] estimated that the incidence of nursing home-acquired pneumonia in the United States may range between 0.3 to 2.3 episodes per 1,000 resident-days. In the present study, we expect to enroll 800 EHPAD residents and follow them over a 12-month period (i.e., a total of 292,000 resident-days). Considering the attrition due to mortality (i.e., 20% per year in this setting^4^), we may expect between 70.1 and 537.3 cases according to the Meher and colleagues’ data [25]. More recently, Rothan-Tondeur and colleagues [38] reported 311 infections in a sample of 2,140 nursing home residents over a period of 28 days (from January 24 to February 20, 2005). The study was conducted defining pneumonia according to the same criteria we will implement in INCUR. Authors showed that pneumonia represented the 7% of all the cases of infections (i.e., 22 events). Translating these figures over a 365-day period (as proposed in the INCUR project) and sample size we plan to recruit (i.e., 800 participants), we obtain 107.2 pneumonia events. It might happen that attrition due to mortality (i.e., 20% per year^4^) and the spring-summer seasons (during which the pneumonia events might be fewer; i.e., additional 40% over 6 months) may further reduce such estimation. However, we believe that, even in the worst case scenario (i.e., 68.6 cases of pneumonia over one year, consistent with the minimum estimation obtained from analyses performed on the Meher and colleagues’ data [25]), it will be possible the evaluation of a sufficient number of events to successfully accomplish the INCUR study aims. The recruited sample size of 800 participants produces a two-sided 98.2% or 95.2% confidence interval with a width equal to 0,050 when the incidence of pneumonia are 10% or 15%, respectively. Such incidence rates are overestimating the outcome of interest compared to the previous study by Rothan-Tondeur et al [38]. (7%); thus, INCUR study is adequately powered to accurately estimate the incidence of pneumonia with the sample of 800 participants.

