c. When a pneumonia event will occur, physical function information collected after its onset will be compared to those previously recorded. The difference in physical function measured before and after the pneumonia event will be adjusted for the days between the event onset and the following physical function assessment. This analytical approach will allow to take into account the negative influence that the presence of a (sub)acute phase of the respiratory process may exert on physical function if the event will occur close to the evaluation. Mixed effects analysis of covariance models will also be performed to evaluate physical function modifications over time between patients who experienced a pneumonia event versus those who did not. If statistical power will be sufficient, stratified analyses will also be performed according to the severity of the pneumonia event (e.g., events requiring hospitalization versus those who did not).

For the present analyses, the sum of the results from the three SPPB categorized tests (ranging from 0 [worst physical performance] to 12 [best physical performance]) as well as the crude timed results obtained from each single assessment (in seconds) will be used for the analyses. This will allow to evaluate whether the pneumonia event will differently affect specific components of physical performance (i.e., balance, muscle strength, or gait/coordination).

Tertiary aims:

a. Chi-square and t-test analyses will be performed to describe the study population for main sociodemographic, behavioral, and clinical characteristics according to the presence/absence of a pneumonia event occurred during the INCUR project follow-up. Mann-Whitney U statistics will be used for non-normally distributed continuous variables. Normalization through log-transformation will be used for non-normally distributed study variables. Subsequent unadjusted and adjusted Cox proportional hazard models will be analyzed to identify patients’ characteristics that are able to significantly predict pneumonia events (dependent variable of interest). Among the covariates, age, gender, race, and preexisting respiratory conditions will always be considered as potential confounders. Age, gender, and race interactions will be tested for the studied relationships by adding specific interaction terms into the models. If possible, stratified analyses will be performed whereas significant interactions will be obtained.

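### Secondary aim c: grouping residents by pneumonia at any time in the year puts a pre-event 0–6 month change in the pneumonia group for about half of the cases

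*Protocol article*

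**What the plan says.** All places are in the protocol article.

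- **Hypotheses and objectives.** Secondary hypothesis c is causal: it holds pneumonia responsible for functional worsening. Secondary aim c measures change in function "according to the presence/absence of a pneumonia event occurred during a follow-up period of 12 months".
- **Methods/design.** Function is assessed at baseline, 6 months and 12 months only. "Recruitment of participants and baseline visits began in February 2012 and ended in July 2012".
- **Analysis plan, secondary aim c, first analysis.** "When a pneumonia event will occur, physical function information collected after its onset will be compared to those previously recorded". The difference is adjusted for the days from onset to the next assessment, so that an assessment made during the acute phase does not mislead.
- **Analysis plan, secondary aim c, second analysis.** Mixed effects analysis of covariance of "physical function modifications over time between patients who experienced a pneumonia event versus those who did not". Nothing in this sentence or in the aim lets a resident's exposure change from visit to visit.

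**The concern.** The mixed model is the only planned analysis of function with a comparison group. It sorts residents by something known only at the end of the year. A resident who develops pneumonia in month 9 belongs to the pneumonia group from baseline, so a 0–6 month change that the pneumonia cannot have caused counts in that group.

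Two biases follow. The later cases show no pneumonia loss at 6 months, which shrinks the 6-month contrast. And if residents who are about to develop pneumonia are already declining, that decline is read as an effect of pneumonia. The second is plausible here: the Discussion describes residents whose equilibrium is already impaired, and the study's case definition accepts a worsening of disability as one of its qualifying signs.

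The before/after comparison does not fill the gap. It uses cases only, so ordinary decline between two visits is counted as loss from pneumonia. Adjusting for days since onset deals with the acute phase, not with ordinary decline.

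**Working it through.** **1. The plan's own event figures (Sample size analyses).** 22 / 2,140 / 28 × 365 × 800 = 107.2. With 20% mortality and 40% fewer events over 6 of 12 months: 107.2 × 0.8 × (1 − 0.4 × 0.5) = 68.6. Both match the article.

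**2. Share L of first events after the 6-month visit.** Inputs from the article: enrolment February–July (taken as uniform), a 40% reduction in spring–summer, 20% yearly mortality. Assumptions: spring–summer means April–September, and yearly incidence is 10% (a value used in the article's precision statement).

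- Constant hazard: L = 1 − (1 − √0.9) / (1 − 0.9) = 1 − 0.513 = 48.7%. At 107.2/800 = 13.4% incidence it is 48.2%.
- Constant hazard with mortality: 0.9 × 0.8 = 0.72, so L = 1 − (1 − √0.72) / (1 − 0.72) = 1 − 0.541 = 45.9%.
- Seasonality: averaged over entry dates, 4.33 of the first 6 months fall in April–September. The first-half weight is 6 − 0.4 × 4.33 = 4.27 out of 12 − 0.4 × 6 = 9.6, so L = 55.6% before allowing for residents who already had a first event. Numerical integration with that allowance gives 54.3%.
- Seasonality with mortality, by numerical integration: 51.6%.

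So L is 46–54%. If each event falls in a different resident, this is about 107.2 × 0.487 = 52 residents (no reductions) or 68.6 × 0.516 = 35 (worst case).

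**3. What the ever/never contrast estimates.** The article gives no effect size or SD for function. Assume a true loss of 1.0 point after onset.

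*No pre-event divergence.* At 6 months: −(1 − L) × 1.0 = −0.54 to −0.46. At 12 months every event has occurred, so the contrast is −1.0. A simulation (800 residents, 13.4% with an event, 400 repeats) agrees:

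| L | 6 months | 12 months |
|---|---|---|
| 0.46 | −0.55 | −1.01 |
| 0.50 | −0.49 | −0.99 |
| 0.55 | −0.44 | −1.01 |

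*Cases decline an extra 0.3 per interval throughout (assumed).* At 6 months: −0.3 − (1 − L) = about −0.8. At 12 months: −0.6 − 1.0 = −1.6. Simulation: −0.76 to −0.84 and −1.60 to −1.61.

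*No true effect, but later cases lose 0.5 in months 0–6 (assumed).* Both visits show −0.5 × L = −0.23 to −0.27.

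**4. The before/after comparison.** With an assumed ordinary decline of 0.3 per interval, a true loss of 1.0 appears as −1.3 and no loss appears as −0.3.

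**5. What interval-based exposure does and does not repair.** Regress the change in each interval on onset within that interval.

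| Scenario | True effect | Estimate |
|---|---|---|
| No pre-event divergence | −1.0 | −1.0 |
| 0.5 decline in an earlier interval only | 0 | 0.0 |
| 0.5 decline inside the onset interval | 0 | −0.5 |
| Extra 0.3 per interval in all cases | 0 | −0.3 |
| Extra 0.3 per interval in all cases | −1.0 | −1.3 |

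In the third row the ever/never average over 6 and 12 months is −0.36 to −0.38, which is nearer to the truth than the recoded estimate. A separate slope for cases repairs the last row: −1.3 − (−0.3) = −1.0. The same slope misleads in the second row. With the second interval of earlier cases coded apart, the only unexposed case intervals are those with the −0.5 decline, so the onset coefficient becomes 0 − (−0.5) = +0.5.

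**The case against.** The strongest points on the other side are these.

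- **The 12-month contrast is intact.** Aim c speaks of a 12-month period, and a model over time yields a contrast at each visit. This stands for dilution. It does not help with pre-event decline, which the 12-month contrast carries in full.
- **Timing was considered.** The onset-aligned comparison comes first and the mixed model is an addition. This deserves credit. But one analysis has timing without a comparator and the other has a comparator without timing, and reading them together does not supply what each lacks.
- **Coding may sit in an analysis plan that is not shown.** This is possible. However, the article does state the grouping, in the aim and again in the analysis, and both wordings refer to having had an event, not to when.
- **Recoding is no cure.** This stands. With visits six months apart, no coding separates decline just before onset from decline just after it.

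A reader might go further in three ways that the documents do not support. One is that at least half of the cases must come after month 6; with the plan's own mortality figure and a constant hazard the share is 46%. Another is that the whole mixed model is diluted; only the 6-month contrast, or an average that includes it, is. The third is that a time-updated exposure isolates the consequence of pneumonia; step 5 shows that it does so only when the earlier decline falls in a previous interval.

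**Conclusion.** The concern holds in this limited form. Followed as written, the only between-group analysis of function counts, for about half of the cases (46–54%), a 0–6 month change that came before the event. Without pre-event divergence the 6-month contrast shows about half of the true effect and the 12-month contrast shows all of it. With pre-event decline both contrasts are contaminated, and at 6 months the two biases pull in opposite directions, so the net error there has no known sign.

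Only the 46–54% rests on documented inputs, together with the assumed April–September season, uniform enrolment and 10% incidence. The loss of 1.0 and the declines of 0.3 and 0.5 are illustrations. Severity is moderate: one secondary aim is affected, and the primary incidence estimate is not.

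**What to change.** Replace the two-group wording for aim c with a visit-level, time-updated exposure:

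1. For each interval (0–6 and 6–12 months), model the change in function on whether onset fell in that interval.
2. Use as comparison the intervals of residents with no onset so far, including the pre-event intervals of later cases.
3. Code the second interval of earlier cases separately as post-event, so that recovery or further decline is mixed with neither exposure nor comparison.
4. Include a resident random effect. Keep the days-since-onset adjustment, applied to exposed intervals only.
5. Adjust for function at the start of the interval and, where available, for prior change. Add a separate case-group slope as a sensitivity analysis only, since it helps with persistent decline and misleads with transient decline.
6. State that decline before onset within the same six-month interval cannot be separated from decline after it, and describe the coefficient as an association, not a proven consequence.

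The cost is small. Onset dates are already needed for the planned days-since-onset adjustment, so this is rewording and recoding with no new data collection. The downside is a somewhat more complex model and residual confounding that has to be acknowledged.

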### Physical function measures

Physical function modifications will be determined by repeated evaluations of several specific scales and questionnaires. In particular, we will use:

1. ADL scale [31]; The number of impaired ADLs was calculated considering the following six tasks: transferring from bed to chair, walking across a room, eating, bathing, using the toilet and personal hygiene.

2. IADL scale [32]; The assessment of impaired IADLs was based on the evaluation of the following four tasks: use of the telephone, use of transportations, managing medications and managing finances.

3. Short Physical Performance Battery (SPPB) [40,41]. The SPPB is a physical performance test composed by three timed subtasks: 4-meter usual gait speed, balance, and chair stand tests. Timed results from each test are scored from 0 (worst performers) to 4 (best performers) according to validated and standardized cut-points [41]. Participants unable to perform a specific SPPB subtest will result with a score of 0 (or the 99th percentile) for that part of the instrument. SPPB has shown to be associated with subclinical (e.g., inflammation, vitamin D, antioxidant status) [42,43] and clinical (e.g., comorbidity, disability, hospitalization, institutionalization, mortality) [44,45] in older persons;

4. Hand grip strength. It will be measured using a hand-held dynamometer (model Jamar). Participants will be asked to perform the task twice with each hand. The average of the best results obtained at each side will be used for the analyses. Hand grip strength has shown to be predictive of health-related events (including disability and mortality) [44,46-48];

5. *Groupes Iso-Ressources* (GIR). According to results of this scale, a special allowance (i.e., *Allocation Personalisée d'Autonomie*, APA) is allocated by the Conseil Général to functionally impaired subjects (scoring 4 or lower). Therefore, its significance is beyond a pure evaluation of physical function, but represents an easy and early indicator of the healthcare cost of an older person.

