### Analysis plan

All the analyses will consider an alpha value threshold equal to 5% as determining the statistical significance.

Primary aims:

a. Taking into account the 12-month follow-up of the study participants, we will detect all the participants experiencing a new pneumonia event. The ratio between the number of participants experiencing one or more events and the number of participants constituing the overall sample will provide the incidence of pneumonia in the sample population. Results will be presented as pneumonia cases per 1,000 resident-days, and as pneumonia events over one year. Stratified analyses will be performed according to age groups, gender, and pre-existing pulmonary disease.

Secondary aims:

a. Primary independent variable of interest for the present analyses will be the total expenditure (in Euros) that participants will cost to the healthcare system over the follow-up year. Additional secondary analyses will also consider specific aspects of the direct healthcare costs of INCUR participants such as expenses due to hospitalizations or physical therapy sessions. All these analyses will be stratified and compared according to the presence/absence of pneumonia events.

Unadjusted and adjusted analyses of covariance, logistic regression models, and multinominal logistic regression models will be performed to evaluate the means and risks of the outcome variables predicted by the absence/presence of pneumonia events occurred during the follow-up (dicothomous independent variable of interest).

b. Participating patients will be divided in two groups, according to the presence/absence of a pneumonia event experienced during the follow-up period. Then, the risk of death will be calculated and compared between the two groups. Kaplan-Meier survival curves will be provided according to pneumonia events. Moreover, adjusted Cox proportional hazard analyses taking into account age, gender, pre-existing pulmonary disease, and other possible confounders will be performed to estimate the risk of dying in patients who experienced a pneumonia versus those who did not. Follow-up will be censored at the date of death for patients dying during the follow-up, or to the last contact date for those who did not.

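### Separate analyses of each SPPB test in crude seconds cannot by themselves show that pneumonia affects balance, strength and gait differently

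*Protocol article*

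**What the plan says.** Under Physical function measures, the article describes the SPPB as "composed by three timed subtasks: 4-meter usual gait speed, balance, and chair stand tests". Under Analysis plan, secondary aim c, the outcomes are the 0-12 sum of the categorized tests, "as well as the crude timed results obtained from each single assessment (in seconds) will be used for the analyses". The next sentence gives the purpose: "This will allow to evaluate whether the pneumonia event will differently affect specific components of physical performance", with balance, muscle strength and gait/coordination named as the components.

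Two analyses are named for aim c. One is a before-after comparison around the event, adjusted for the days from onset to the next assessment. The other is a comparison of groups: "Mixed effects analysis of covariance models will also be performed to evaluate physical function modifications over time between patients who experienced a pneumonia event", against those who did not.

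A general sentence opens the Analysis plan: "All the analyses will consider an alpha value threshold equal to 5% as determining the statistical significance". The only interactions named are under tertiary aim a: "Age, gender, and race interactions will be tested for the studied relationships by adding specific interaction terms into the models".

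**The concern.** The question whether components are affected differently is a comparison between components. The analyses named answer another question, asked of one function measure at a time: did it change, or did it differ by pneumonia status?

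The coefficients cannot be set side by side either. A second of balance time, of chair-stand time and of walking time are different quantities, and better performance is a longer time on one test and a shorter time on the others. Residents who cannot do a test receive an assigned value (score 0, or the 99th percentile), so the crude result on each test also depends on how many fail it.

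The risk is a published statement such as 'gait affected, balance spared' that reflects chance and limited power. A non-significant component could be taken as unaffected.

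**Working it through.** **1. What the named analyses estimate**

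| Element of aim c | Contrast it gives | Between components? |
|---|---|---|
| Function before and after the event | time, among cases | no |
| Mixed-effects analysis of covariance | pneumonia versus none, over time | no |
| Crude seconds for each test | choice of outcome, three scales | no |

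No contrast between components, component-by-pneumonia term or common scale is named.

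**2. Group sizes from the article (Sample size analyses)**

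The article's expected event counts reproduce:
- US incidence range: 292,000 × 0.3/1,000 × 0.8 = 70.1, and 292,000 × 2.3/1,000 × 0.8 = 537.3.
- French survey: 22/2,140 × 365/28 × 800 = 107.2.
- Worst case: 107.2 × 0.8 (mortality) × 0.8 (40% fewer over half the year) = 68.6.

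Survivors at 20% mortality: 800 × 0.8 = 640.

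Assumed assessable cases: 0.8 × 68.6 ≈ 55 and 0.8 × 107.2 ≈ 86, leaving 585 and 554 residents without pneumonia. The 68.6 already contains one mortality reduction. The second factor of 0.8 assumes that further cases die before they are reassessed.

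**3. If a difference were read from which tests reach 5%**

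This reading is inferred; the article does not state it. Two-sided tests are assumed. For a common standardized effect d on all three tests:

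- δ = d / √(1/n₁ + 1/n₂)
- power per test = Φ(δ − 1.96) + Φ(−δ − 1.96)
- P(tests disagree) = 1 − P(all three significant) − P(none significant), with equally correlated normal test statistics

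Worked case, 55 versus 585, d = 0.3, correlation 0: √(1/55 + 1/585) = 0.141; δ = 2.13; power = 0.566; 1 − 0.566³ − 0.434³ = 0.74.

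Chance of disagreement when the effects are identical, by correlation:

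| Groups | d (SD) | Power per test | 0 | 0.3 | 0.5 | 0.7 |
|---|---|---|---|---|---|---|
| 55 v 585 | 0.2 | 29% | 62% | 51% | 43% | 33% |
| 55 v 585 | 0.3 | 57% | 74% | 60% | 49% | 37% |
| 55 v 585 | 0.4 | 81% | 46% | 39% | 33% | 25% |
| 55 v 585 | 0.5 | 94% | 16% | 14% | 13% | 10% |
| 86 v 554 | 0.2 | 41% | 72% | 59% | 49% | 37% |
| 86 v 554 | 0.3 | 74% | 58% | 48% | 40% | 31% |
| 86 v 554 | 0.4 | 93% | 19% | 17% | 15% | 12% |
| 86 v 554 | 0.5 | 99% | 3% | 3% | 2% | 2% |
| either | 0 | 5% | 14% | 14% | 12% | 10% |

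**4. Upper event estimate**

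0.8 × 537.3 ≈ 430 cases versus 210 others. This treats episodes as distinct residents, which overstates cases if episodes recur. Disagreement is 10-15% at 0.3 SD and below 1% at 0.4 SD, but still 35-67% at 0.2 SD (power 66%).

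**5. Direct comparison**

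A 2-df Wald test of equal standardized effects, simulated with 300,000 draws at about 80% power per test, rejects in 5.0-5.1% of studies at correlations 0.3, 0.5 and 0.7. Reading from the separate tests gives 40%, 34% and 26% in the same draws.

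The power figures use a two-group normal approximation and ignore clustering by nursing home and covariate adjustment.

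**The case against.** The strongest reply is that the article never states a rule of reading differences from discordant p-values. It says that the outcomes will be used and that this permits an evaluation. The 5% sentence is a general statement of alpha. A condensed article may leave the exact contrast to a fuller plan, and tertiary aim a shows that the authors know how to use interaction terms. This stands as far as the rule goes: the error rates in the working are conditional on an inferred reading. It does not remove the point, because the article asserts that these outputs answer the between-component question, and as described they do not.

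A reader might infer that the plan yields a false difference in about half of studies. The documents do not support such a figure. It depends on effect size, correlation and number of cases, none of which is given for the SPPB tests, and the result runs from 2% to 74% over the assumptions used here. Three tests in the same person may well be strongly correlated, which lowers it.

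A reader might also extend the point to the stratified analyses by severity of pneumonia (hospitalized or not). The text does not support that. Those analyses are conditional on sufficient power, and no claim is made that strata will be shown to differ.

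Two further points are fair. Equal effect across different tests has no unique definition, so the 5% rate of the direct test holds only for the scale chosen. And the stakes are limited: this is a sub-question of one secondary aim in an observational study, and neither the primary aim nor the sample size depends on it.

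**Conclusion.** The concern holds in this form: the analyses stated for secondary aim c cannot alone support the differential inference attached to them, because no comparison between components is named and crude seconds have no common scale. This follows from the text and needs no assumption.

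The size is conditional. It rests on the inferred reading and on the assumed case numbers, effects and correlations in the working. Disagreement far exceeds 5% for small to moderate effects. At 0.5 SD with 86 cases it falls below 5%. With cases near the article's upper estimate it is lower from 0.3 SD upward, but not at 0.2 SD.

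**What to change.** In secondary aim c, put the three components on one scale with the same direction, for example baseline-SD units, and state that this scale defines what an equal effect means. Fit them jointly by extending the planned mixed model, and base any statement that components are affected differently on the component-by-pneumonia interaction (2 df) with confidence intervals.

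Alternatively, report the three separate effects with confidence intervals and delete the sentence claiming that they show a differential effect.

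The cost is one added model on data already collected, or a change of wording. The downside is that the interaction test has limited power and its result depends on the chosen scale, so fewer differential statements will be possible.
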